### Criteria for discontinuing or modifying allocated interventions {11b}

No harmful effect is anticipated for children, so there is no reason to stop the trial by itself or to change allocation. The only change that may occur is the adaptation of messages due to external circumstances.

### Strategies to improve adherence to interventions {11c}

Protocol was developed with school stakeholders. Also, documents were developed with the involvement of the children. For the first leaflets for the children, a pre-test was undertaken in a voluntary school, not included in the trial; their overall perception and understanding of the wording led to the adaptation of the content. Also, the intervention documents have been successively developed, each one considering the feedback potentially received from the precedent document.

### Relevant concomitant care permitted or prohibited during the trial {11d}

All schools, from the intervention groups and the control group, are free to continue their ongoing projects about nutrition and sustainability.

### Provisions for post-trial care {30}

There is no anticipated harm and compensation for trial participation.

### Outcomes {12}

The first quantitative judgement criterion will be the change over time in the mean SB consumption (in ml/day) in the intervention groups compared with the control group (Fig. 1). The secondary criteria of judgement will be the change in the proportion of children consuming SB each day on the one hand and in the mean consumption of water (in ml/day) on the other hand. Quantitative outcomes in ml/day will be evaluated through a 4-day booklet, while the daily consumption will be based on a short frequency questionnaire. These outcomes will be measured at the second wave of data collection and changes estimated by difference with the pre-intervention measurements. Findings at the first post-intervention data collection will also be presented once the trial is finished.

Among the secondary objectives of the DRINK trial, the same outcomes will be used to assess the potential interaction between nutrition- and sustainability-based interventions (Fig. 1). The other three secondary objectives will be assessed using complementary information as described below. Altogether, the information collected and the regular monitoring of the trial development (including cost which is one of the objectives) will also enable to develop a comprehensive process evaluation.

### Participant timeline {13}

Despite the COVID-19 impact on schools’ organisation in 2021, the agenda of the research is maintained as initially planned (Figs. 3 and 4). Recruitment and first assessment, prior to randomisation and intervention, were planned to be held in the second period of the school year 2020–2021 for all schools. In essence, they were implemented in May to June 2021 but continued in the beginning of the next school year, due to the lack of availability of some school staff (Fig. 3). Therefore, two cohorts have been formed, including 26 schools and 22 schools, respectively.

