**Methods:**

Forty-eight French-speaking Belgian primary schools (equivalent to around 3500 pupils involved in the evaluation) are randomised using a factorial plan: (i) control, (ii) nutrition-based intervention, (iii) sustainability-based intervention, and (iv) both. The interventions (encouragement of water breaks; provision of posters, leaflets, reusable cups, and glass bottles; website; meetings at school) were undertaken from February 2022 to June 2023. Evaluation includes questionnaires for the children and their parents on various determinants of dietary behaviour, a 4-day diary to collect information on the child’s beverage consumption, and audits at schools. The first evaluation was conducted in Spring 2021 before any intervention, with the two post-intervention evaluations being held in 2022 and 2023. The main quantitative judgement criterion will be the change over time in the mean SB consumption (in ml/day) in the intervention groups compared with the control group. Given the context of the research (school), the safety of the intervention, and the content of data collection, a consent was acknowledged as unnecessary by the Ethical Committee of the Faculty of Psychology (ULB; n°073/2021), but children and parents are explicitly informed of their right to refuse to fill in the questionnaires.

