**Fig. 4 Fig4:**
[figure not shown]
Participant timeline

For a given child, follow-up will vary depending on his/her grade at entry in the DRINK trial. Children in 3rd and 4th grades (8 to 10 years of age) at inclusion will be followed up during two school years (5th–6th grades at the endpoint, when they are 10 to 12 years old), with an intermediate assessment after 1 year. Those who were schooled in 5th grade at the first evaluation will be followed up for 1 year and will contribute to the intermediate assessment of effectiveness only. Exposure to intervention will be considered as “continuous” during the two school years since actions will have been implemented steadily.

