## Assignment of interventions: allocation

### Sequence generation {16a}

After the first wave of data collection, we assigned the schools to the four groups. All schools were randomly numbered (“rununiform” command in Stata®), and allocation was made by dividing the schools into 4 equal groups. The allocation process was blinded to any information related to schools in an independent database.

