## Trial status

The first wave of data collection took place in Spring and Autumn 2021, and the second wave was just finished at the beginning of 2023. The third and last wave of data collection is planned for the period from April to December 2023. The main results will be disseminated by the end of 2024, through publications and conference communications.

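### The primary endpoint pools schools measured during the intervention with schools measured after it ended, and the plan does not commit to adjusting for, or reporting by, baseline cohort

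*Protocol article*

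**What the plan says.** Participant timeline {13} explains that recruitment and first assessment, planned for one period, ran on into the following school year: "Therefore, two cohorts have been formed, including 26 schools and 22 schools, respectively". Trial status confirms it: "The first wave of data collection took place in Spring and Autumn 2021". The abstract still gives Spring 2021 as the only baseline date.

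The abstract says the interventions "were undertaken from February 2022 to June 2023". Trial status adds that "the second wave was just finished at the beginning of 2023" and "The third and last wave of data collection is planned for the period from April to December 2023".

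Participant timeline {13} also requires children who enter in 3rd or 4th grade to be in 5th or 6th grade at the endpoint. It treats exposure as continuous "during the two school years since actions will have been implemented steadily".

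On allocation, Sequence generation {16a} says that after the first wave the schools were randomly numbered and "allocation was made by dividing the schools into 4 equal groups". It adds: "The allocation process was blinded to any information related to schools in an independent database". No stratum is mentioned.

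The primary analysis ({20a}) is one multilevel model of each child's change from baseline to endpoint, over all schools. Section {20b} chooses adjustment variables from the differences seen between randomised groups at inclusion. It lists stratified analyses by weight status, family socio-economic status and school indicators such as socio-economic index and province. Cohort appears in neither.

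**The concern.** The split is more than a delay in fieldwork. With one common intervention calendar and a grade rule that counts school years from each child's entry, the two cohorts sit at different points of the intervention when they are measured. The primary estimate then averages an effect seen while water breaks and materials are in place with an effect seen some months after they stopped. A reader told that exposure was continuous would not know this.

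Separately, cohort is a known school-level feature, fixed before allocation, that may be related to the change in consumption. If it is neither balanced by design nor committed to the model, the trial accepts avoidable variance. Whether cohort is adjusted for would also depend on how the observed imbalance looks, which is a weaker rule than naming it in advance.

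**Working it through.** **1. The plan's own sample size.** Inputs from Sample size {14}: 200 v 170 ml/day (difference 30), SD 120, alpha 5% (taken as two-sided), power 80%, ICC 0.08, 4 × 17 = 68 pupils per school.
- Per side without clustering: 2 × (1.960 + 0.842)² × 120² / 30² = 251.2, so 252.
- Design effect: 1 + 67 × 0.08 = 6.36. Then 252 × 6.36 / 68 = 23.6, so 24 schools per side. That is 48 schools and 3264 pupils, against the stated 48 and around 3200. It reproduces.
- School-level variance: 0.08 × 14400 + 0.92 × 14400 / 68 = 1152 + 194.8 = 1346.8. SE of a 24 v 24 contrast: √(2 × 1346.8 / 24) = 10.59 ml/day. Power: Φ(30/10.59 − 1.96) = 80.8%.

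**2. Where each cohort stands at each wave.** I take the school year as September to June and assume no repeated grades. The wave 2 row also assumes re-measurement about a year after baseline.

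| | Spring cohort (26 schools) | Autumn cohort (22 schools) |
|---|---|---|
| Baseline | May–June 2021, before intervention | Autumn 2021, before intervention |
| Wave 2 | By June 2022, about 3–5 months after the start | Autumn 2022 to early 2023, about 7–12 months after the start |
| In 5th–6th grade | School year 2022/23 | School year 2023/24 |
| Wave 3 | April–June 2023, actions still running | September–December 2023, about 2–6 months after they ended |

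The wave 3 row follows from the grade rule and the stated collection window. In April–June 2023 the autumn entrants are still in 4th–5th grade. After June 2023 the spring cohort's 4th-grade entrants have left 6th grade. Trial design {8} runs the trial to 2023/2024, which agrees.

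**3. Chance imbalance of cohort.** With 48 schools, 26 of them spring, and 24 on each side of a main effect, the number of spring schools on one side is hypergeometric.
- Mean 13; variance 24 × (26/48) × (22/48) × (24/47) = 3.04; SD 1.744.
- SD of the difference in spring share: 2 × 1.744 / 24 = 0.145.
- Probability of 15 v 11 or worse, in either direction: 39%. Of 16 v 10 or worse: 15%.

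**4. What that costs.** Let D be the difference between cohorts in mean change. The documents give no value, so a range is assumed. The shift in the effect has mean zero and SD 0.145 × D. Power is Φ(30/√(10.59² + (0.145D)²) − 1.96).

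| Assumed D (ml/day) | SD of shift (ml/day) | Power |
|---|---|---|
| 10 | 1.5 | 80.1% |
| 20 | 2.9 | 78.0% |
| 30 | 4.4 | 74.5% |

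Adjusting for cohort returns power to about 80.8%.

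**5. What adjustment does not remove.** If autumn schools keep a fraction f of a 30 ml/day effect once actions have stopped, the pooled effect is 30 × (26 + 22f)/48. For f = 0.75 it is 26.6 ml/day (power 71%); for f = 0.5 it is 23.1 ml/day (power 59%). Both values of f are assumptions. They show why a result by cohort is needed as well as a covariate.

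**6. How well cohorts can be compared.** With about 13 v 13 spring and 11 v 11 autumn schools, the SE of an intervention-by-cohort term is √(1346.8 × (2/13 + 2/11)) = 21.3 ml/day, twice that of the main effect. It can describe a difference but has little power to test one.

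**The case against.** Much of the opposing case stands.

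- *No bias.* From pooled cohorts with different baselines a reader might infer a biased effect. Cohort was fixed before random allocation, so it is independent of group and any shift averages zero.
- *Season.* A stable seasonal level cancels in a within-child change if each cohort is re-measured in its own season, which is what the grade rule implies for wave 3.
- *Status at every wave.* A reader might infer that intervention status differs throughout. It does not: both cohorts were untreated at baseline and both were within the intervention period at wave 2. Only the duration of exposure differs at wave 2; status differs at wave 3.
- *Scheduling.* The nine-month wave 3 window might suggest that spring schools could slip past June 2023 and lose their older pupils. No passage says so, and Fig. 3, which is not shown, may set the dates by cohort.
- *Allocation.* It might have been done within cohort: 7+7+6+6 and 5+5+6+6 give 12 schools per group. Step 3 would then overstate the imbalance. The text reads more naturally as one draw and mentions no stratum.
- *Exposure statement.* It enters no model, since the analysis is by intention to treat. Correcting it changes interpretation, not an estimate.
- *Covariates.* A covariate list is commonly left to the analysis plan, and the adjustment rule could pick up cohort. But the article does state a rule, and that rule depends on observed imbalance.

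**Conclusion.** The point holds as one of precision and interpretation. The pooled primary change averages an on-intervention effect (26 schools) with a post-intervention effect (22 schools), and the article describes exposure in a way its own dates do not bear out. Cohort is left to a data-driven covariate rule. The cost in power is about 0.7 to 6 points for an assumed 10–30 ml/day cohort difference in change, and is small at the lower end. Larger shifts would need a cohort difference above the whole planned effect of 30 ml/day, for which the documents offer no support.

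The wave 3 timing rests on the stated dates and the grade rule. The wave 2 exposure figures rest also on re-measurement about a year after baseline. The imbalance figures rest on allocation having been a single unstratified draw. The change is worth making because it costs almost nothing and can be fixed before the data are analysed.

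**What to change.** 1. Include cohort (spring or autumn 2021) as a fixed covariate in every primary and secondary effectiveness model, whatever imbalance is observed. Cost: one school-level degree of freedom out of 48 schools.
2. Report the intermediate and final effects by cohort, with an intervention-by-cohort term. Label this a secondary analysis of low power, and give the months from the start and from the end of the intervention to the diary for each cohort. Cost: one table.
3. Reconcile the exposure statement in Participant timeline {13} and the Spring 2021 baseline in the abstract with the two cohorts and the wave dates under Trial status. Say plainly that the pooled endpoint covers both on-intervention and post-intervention measurement. Cost: a few sentences.

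No change to the measurement schedule is asked for, since it may already be set by cohort in Fig. 3.

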**Fig. 3 Fig3:**
[figure not shown]
Timeline of the DRINK trial (measurements, randomisation, interventions)

**Fig. 4 Fig4:**
[figure not shown]
Participant timeline

For a given child, follow-up will vary depending on his/her grade at entry in the DRINK trial. Children in 3rd and 4th grades (8 to 10 years of age) at inclusion will be followed up during two school years (5th–6th grades at the endpoint, when they are 10 to 12 years old), with an intermediate assessment after 1 year. Those who were schooled in 5th grade at the first evaluation will be followed up for 1 year and will contribute to the intermediate assessment of effectiveness only. Exposure to intervention will be considered as “continuous” during the two school years since actions will have been implemented steadily.

### Sample size {14}

The sample size determination is based on the cluster-randomised factorial plan [45, 46]. The following assumptions have been set for the first criterion of judgement: (i) observed mean of SB consumption, i.e. 200 ml/day (SD: 120 ml) [47]; (ii) a 15% reduction in the intervention group (either nutrition or sustainability), i.e. mean 170 ml/day at the last 2-year follow-up and stability in the control group; (iii) type I error (alpha) of 5%; (iv) statistical power of 80%; and (v) intra-class correlation of 0.08 (estimation based on the “Health Behaviour in School-aged Children” (HBSC) survey carried out in 2018 in French-speaking Belgian primary schools) [48]. The theoretical total number of schools needed is estimated at 48, corresponding to around 3200 students surveyed during the 2 years (based on the same 2018 HBSC survey: on average, four classes in each participating school and 17 students in each of these classes). Since we use a factorial plan, 12 schools are allocated in each group (Fig. 1).

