### Eligibility criteria {10}

All schools under the aegis of the Ministry of Education (FWB) were eligible, the exception being those solely for children with disabilities or special needs. The design of the study requiring to follow students during two school years and for organisation reasons, schools not having students in 3rd to 6th grades, and those with less than 11 students by grade were excluded from the selection. Among the participating schools, all children schooled in the 3rd to 5th grades (8 to 10 years of age) at the initial evaluation were eligible unless they had important difficulties in reading and understanding French (such as some foreign children who have just arrived in Belgium).

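### The sample size counts about 3200 pupils at 2 years, but 5th graders cannot reach that endpoint, no loss is allowed for, and the SD is not that of the analysed change; the effect on power is small or undetermined

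*Protocol article*

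**What the plan says.** All references are to the protocol article.

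- **Sample size {14}.** The inputs are "observed mean of SB consumption, i.e. 200 ml/day (SD: 120 ml"), a 15% reduction to "mean 170 ml/day at the last 2-year follow-up and stability in the control group", alpha 5%, power 80%, an intra-class correlation of 0.08, and on average four classes of 17 pupils per school. The result is: "The theoretical total number of schools needed is estimated at 48, corresponding to around 3200 students surveyed during the 2 years". Twelve schools go to each of the four groups. No allowance for loss is mentioned.
- **Eligibility criteria {10}.** Three grades are enrolled: "all children schooled in the 3rd to 5th grades (8 to 10 years of age) at the initial evaluation were eligible", apart from those with major difficulty in French.
- **Participant timeline {13}.** Pupils in 3rd and 4th grade at inclusion are followed for two school years. Those in 5th grade "will be followed up for 1 year and will contribute to the intermediate assessment of effectiveness only".
- **Abstract, Methods.** "Forty-eight French-speaking Belgian primary schools (equivalent to around 3500 pupils involved in the evaluation").
- **Outcomes {12} and Statistical methods {20a}.** The primary outcome is the change in consumption to the 2-year wave, computed as endpoint minus baseline for each child followed over that period.
- **Discussion.** Long follow-up may lower school participation, some children may change schools, and completion of the 4-day booklets is expected to be lower than interviews would give.

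**The concern.** Section {14} powers a 2-year comparison, but its inputs do not describe the 2-year analysis in three respects. One of the three enrolled grades cannot enter that analysis. Loss is foreseen in the Discussion but has no place in the calculation. The SD describes a level of consumption, while {20a} analyses a within-child difference.

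At stake is how the result will be read. The Discussion presents the sample size as a methodological strength. If the published justification claims more children than can contribute, and a power not tied to the analysed outcome, a null or imprecise 2-year result could be given more weight than the design supports.

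**Working it through.** **Reproducing the stated figure.** Inputs from {14}: difference 200 − 170 = 30 ml/day, SD 120, two-sided alpha 5%, power 80%, intra-class correlation 0.08, pupils per school m = 4 × 17 = 68. The sides of alpha are not stated; a one-sided test gives about 37 schools and does not fit.

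- Unclustered n per side = 2 × (1.96 + 0.8416)² × 120² / 30² = 251.2
- Design effect = 1 + (68 − 1) × 0.08 = 6.36
- Schools per side = 251.2 × 6.36 / 68 = 23.5, rounded up to 24
- Total = 48 schools and 48 × 68 = 3264 pupils

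This matches 48 schools and about 3200 pupils. It does so with every one of the 68 pupils analysed and no inflation for loss. Each factorial main effect compares 24 schools with 24.

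**Children who can reach the 2-year endpoint.** Assumptions: the three grades are of equal size, and the pupil counts cover all three.

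- From 68 per school: 68 × 2/3 = 45.3 per school, 48 × 45.3 ≈ 2180
- From 3500 pupils: 3500 / 48 = 72.9 per school, × 2/3 = 48.6, 48 × 48.6 ≈ 2330

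Both are before any loss, and 27% to 32% below 3200.

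**Power for 30 ml with 48 schools.** Effective n per side = 24m / (1 + (m − 1) × 0.08). SE = 120 × √(2 / effective n). Power = Φ(30/SE − 1.96). Detectable difference at 80% power = 2.80 × SE. The SD of change is taken as 120 here. The loss rates are assumptions, since the article gives none.

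| Pupils per school | Situation | Effective n per side | SE (ml) | Power | Detectable difference |
|---|---|---|---|---|---|
| 68 | as in {14} | 256.6 | 10.59 | 80.8% | 29.7 ml |
| 48.6 | two grades, from 3500 | 242.6 | 10.90 | 78.6% | 30.5 ml |
| 45.3 | two grades, from 68 | 239.3 | 10.97 | 78.1% | 30.7 ml |
| 38.9 | 48.6 with 20% loss | 231.5 | 11.15 | 76.7% | 31.2 ml |
| 34.0 | 48.6 with 30% loss | 224.2 | 11.33 | 75.4% | 31.8 ml |
| 31.7 | 45.3 with 30% loss | 220.2 | 11.44 | 74.6% | 32.0 ml |

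A t-test on 46 degrees of freedom lowers each power by about 2 points, including the starting figure (79.2% at 68 per school).

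**SD of the analysed change.** With equal variances at both waves and baseline-to-endpoint correlation r, the SD of change = 120 × √(2(1 − r)). The article gives no r. At 48.6 per school, no loss, and the intra-class correlation of 0.08 carried over to the change:

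| r | SD of change | Power |
|---|---|---|
| 0.3 | 142.0 | 64% |
| 0.4 | 131.5 | 71% |
| 0.5 | 120.0 | 79% |
| 0.6 | 107.3 | 87% |

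Power returns to 80% at about r = 0.52 with no loss, and at about r = 0.56 for 45.3 per school with 30% loss.

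**The case against.** The strongest reply is that the arithmetic in {14} is correct and that the children lost matter little. With an intra-class correlation of 0.08, a school's effective contribution falls only from 68/6.36 = 10.7 to 48.6/4.81 = 10.1, about 5.5%, so a 27% shortfall in headcount overstates the statistical loss. This stands.

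A second reply is that {14} does not say which grades the four classes cover. If the 68 were 3rd and 4th graders only, the grade argument against the calculation itself would fall away. Also, being surveyed during the 2 years is not literally being analysed at 2 years. The ambiguity is real. However, 3500 pupils in 48 schools is about 73 per school, close to 68 and consistent with 68 being the whole enrolled group. If the 3500 span three grades, about 2330 children can reach the endpoint however the four classes are read.

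A third reply is that all loss rates used here are assumed. That is true. The Discussion expects loss but quantifies none, so only the absence of an allowance is firm.

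A reader might go further and infer that 80% power is not delivered, or that the SD of change is probably above 120 ml. The documents do not support either. They give neither r nor the intra-class correlation of the change. The low values in the second table hold only for the r chosen, and r = 0.6 gives 87%. A model adjusted for baseline, with SD 120 × √(1 − r²), would regain 80% at about r = 0.19 with no loss (48.6 per school, intra-class correlation 0.08).

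**Conclusion.** The point holds for the pupil count and for the basis of the power statement. The 3200 pupils are not met at the 2-year endpoint: about 2200 to 2330 can reach it before loss, given equal grades and pupil counts that cover all three. The 80% is not tied to the planned analysis. If the SD of change is 120 ml and the intra-class correlation 0.08, power is about 78% with no loss (detectable difference about 30.5 ml) and about 75 to 77% with an assumed 20 to 30% loss (about 31 to 32 ml). The SD mismatch is a genuine gap of unknown direction: power is lower if r is below 0.5 and reaches 80% or more above roughly 0.52 to 0.56.

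This is a minor to moderate correction to the stated justification. It does not affect the allocation or the planned analysis.

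**What to change.** Restate {14} for the analysis in {20a}:

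1. Count only children in 3rd or 4th grade at entry, say which grades the four classes cover, and reconcile the 3200 with the 3500 in the Abstract.
2. Include the expected completion of both diaries over 2 years.
3. Use the SD of the analysed quantity, with r and the intra-class correlation taken from the diaries pooled over groups.
4. Report the resulting power or detectable difference for 48 schools in place of 80% and 3200 students.
5. State that the 2-year conclusion covers children who were in 3rd or 4th grade at entry.

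The cost is one recalculated paragraph and possibly a slightly less favourable figure. No extra recruitment is needed, and pooling over groups keeps the allocation blinded.
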